#### Postnatal mother-infant relationship

##### Postnatal attachment

Postnatal maternal emotional attachment is measured using the Maternal Postnatal Attachment Scale (MPAS), which is a validated 19-item postpartum counterpart of Condon’s MAAS [84]. It measures the mother’s reported feelings about her infant by three factors: (1) quality of bonding, (2) absence of hostility, and (3) pleasure in interaction [87]. A higher score indicates a more adaptive mother-infant bonding style [87].

The MPAS questionnaire is filled out electronically by REDCap in connection with the postpartum interaction observation visit. After their recruitment, the participants individually receive the links to the electronic questionnaires.

##### Mother-infant interaction

The quality of the mother-infant interaction is assessed using the Parent-Child Early Relational Assessment (PCERA) [88, 89], a video-observation method. The interaction situations are recorded by the graduate students in psychology 4–5 months postpartum. In the current study, the mother-infant interaction is video-recorded during a free-play session using a standardized set of toys. The videos are recorded in a laboratory setting to standardize the environment. The situations are analyzed according to the PCERA manual [89], which consists of 65 independent items: 29 parental, 28 children, and eight dyadic items. Ratings are based on a 5-min interactions sequence. The items are scored from 1 to 5; scores 1 and 2 represent an area of concern, 3 denotes an area of some concern, and 4 and 5 signify an area of strength. Two trained coders who have achieved an appropriate level of reliability, with more than 80% agreement with a trainer of the method, analyze the quality of the interaction according to the manual. The method has good factorial validity and evidence for convergent and discriminant validity as well [88, 90].

### Plans to promote participant retention and complete follow-up {18b}

Participant retention can be strengthened by phone calls or short message service as needed.

### Data management {19}

A data file description is required by the Ethics Committee of the Hospital District of Southwest Finland in order to obtain research permission. The participants’ files are preserved separately from the research data in a secure place. The participants are assigned ID codes that will be used for data storage and analysis. The research data are pseudoanonymized: the recruitment log of the participants is used to undo the ID codes and is kept separately from the data files. The form data are stored in REDCap [70], which, in turn, is stored in a secure network drive of the University of Turku. The videotapes are stored in a secure online storage of the University of Turku.

The University of Turku automatically provides copies of the research data into three independent servers when the data are stored. The servers also function as a data backup system. Only the members of the study group have access to the data. Access to the storage is controlled by the principal investigator of the study. Access also requires a personal username issued by the University of Turku. The allowed access to the data is issued only for the active research period. The principal investigator keeps a record of those who have active access to the data. All the data will be disposed of 10 years after the last publication.

### Confidentiality {27}

See the “Data management {19}” section.

### Plans for collection, laboratory evaluation, and storage of biological specimens for genetic or molecular analysis in this trial/future use {33}.

These are not applicable. No biological specimens are collected in this study.

## Statistical methods

### Statistical methods for primary and secondary outcomes {20a}

The categorical variables of the study are characterized using frequencies and percentages. Continuous variables with means and SDs or medians with ranges and/or 25th and 75th percentiles are used. Age is summarized with the mean and the range.

If the assumptions for parametric analyses are met, the mean change of the EPDS score over time is analyzed using a linear mixed modeling approach for repeated measures. Then, the time point is considered as a within-factor and the treatment intervention as a between factor-effect. The effects of the participants’ background variables’ parity, age, antidepressant medication, care contacts within healthcare, and so forth, are also tested. The time point x intervention interaction describes whether the mean changes over time differ between the groups. The covariance structure of the unstructured (UN) and the compound symmetry (CS) is tested. The differences (together with 95% confidence interval [CI]) between the groups are also estimated at each time point, as well as within-group changes. Transformation for the EPDS or for other outcomes can be performed before analyses, if needed. The assumptions of parametric tests are checked using studentized residuals for justification of the analyses. Other numerical variables, mean change of MAAS, MPAS, SCL-90, and PRAQ-R2 score over time, are analyzed in a similar way.

*P*-values less than 0.05 are considered statistically significant (two-tailed). Statistical analyses are performed using SAS System for Windows, Version 9.4 or later (SAS Institute Inc., Cary, NC, USA).

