### Eligibility criteria {10}

The inclusion criteria are as follows:(1) 10–15 points on the EPDS, (2) singleton pregnancy, (3) over 18 years of age, (4) body mass index under 35, and (4) fluency in the Finnish language.

The exclusion criteria are psychotic and self-destructive symptoms. The use of antidepressant medication is not an obstacle to participation.

The women are recruited after the routine screening for severe structural abnormalities between 19 and 21 gwks offered by the municipalities. Severe structural abnormalities are an exclusion criterion.

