### Outcomes {12}

The primary outcome of the study is perinatal depressive symptoms analyzed as a change in the EPDS- mean score from before the intervention to after the intervention, maternal attachment, and prenatal representations before and after the intervention. The secondary outcomes are maternal-infant-relationship- related outcomes; maternal pregnancy-related psychological distress, and mother-infant interaction. The secondary outcomes are analyzed with both quantitative and qualitative methods.

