### Sample size {14}

The study aims to compare changes in EPDS scores between two independent groups. A mean decrease of three points in the EPDS score is considered clinically relevant and used for power calculations. A standard deviation (SD) of 3.5 points in the EPDS score used in power calculations was based on earlier studies in the Finnish population showing an SD of 3.7–4 [25]. A power analysis using a statistical power of 80% and a significance level of 0.05 (two-tailed) showed that 50 subjects are needed in both groups. Because of an estimated attrition rate of 10%, 60 subjects for both groups are currently being enrolled. Randomization was performed with random permuted blocks, using block size 10. The SAS® was used to generate the randomization (Version 9.4 for Windows).

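### The EPDS mixed model leaves pre-randomisation EPDS as a free response in each group; adjusting for it would be valid, free and at least as precise

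*Protocol article*

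**What the plan says.** The section on statistical methods {20a} fits a linear mixed model for repeated measures to EPDS. Its structure is given as: "Then, the time point is considered as a within-factor and the treatment intervention as a between factor-effect". The time point by intervention interaction shows whether mean changes differ between the groups. Background variables enter loosely: "parity, age, antidepressant medication, care contacts within healthcare, and so forth, are also tested". Baseline EPDS is not on that list, and no common baseline mean is stated. On covariance, "The covariance structure of the unstructured (UN) and the compound symmetry (CS) is tested". MAAS, MPAS, SCL-90 and PRAQ-R2 are to be analysed in a similar way.

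The section on depressive symptoms (under {18a}) gives three EPDS time points, tied to the two prenatal interviews and the postpartum visit. Trial design {8} places randomisation after the first interview, so the first of these is a true baseline.

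Outcomes {12} says that depressive symptoms are "analyzed as a change in the EPDS- mean score from before the intervention to after the intervention". Sample size {14} agrees: "The study aims to compare changes in EPDS scores between two independent groups". Eligibility {10} requires "10–15 points on the EPDS", which Recruitment {15} shows to be the score on the web-based screening questionnaire.

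**The concern.** When time and group are both free factors, the model estimates a separate baseline mean for each group. These groups were formed by randomisation after the baseline was taken, so any baseline difference is chance. The interaction subtracts that chance difference in full. It should be removed only to the extent that baseline predicts follow-up. If the slope of follow-up on baseline is below 1, subtracting the whole difference adds noise.

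At stake is precision, not validity. The confidence interval for the primary EPDS comparison may be wider than the collected data allow. A smaller, related issue is that an open list of variables to be tested does not settle which covariates belong in the primary model.

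**Working it through.** **Inputs from the protocol.** The planning effect: "A mean decrease of three points in the EPDS score is considered clinically relevant and used for power calculations". The SD: "A standard deviation (SD) of 3.5 points in the EPDS score used in power calculations was based on earlier studies", where the earlier studies showed 3.7–4. Two-sided alpha is 0.05, power 80%, and 50 women per group.

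**Inputs not in the protocol (assumptions).** The correlation r between first- and second-interview EPDS, taken as 0.3–0.7, and the SD at each visit, s1 at baseline and s2 at follow-up.

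**The plan's own figure.** n per group = 2 × (1.96 + 0.84)² × 3.5² / 3² = 21.4, so 22. The stated 50 is not reproduced from these inputs. That is a separate matter. It matters here only because 50 per group is generous for a 3-point effect.

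**Variance of the two contrasts (per woman, complete data, large sample).**
- Change score: s1² + s2² − 2·r·s1·s2
- Baseline-adjusted: s2²·(1 − r²)
- Difference: (s1 − r·s2)², which is never negative. It is zero only when s1 = r·s2, that is, when the slope of follow-up on baseline is 1.

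**Equal SDs.** The share saved is 1 − (1 − r²)/[2(1 − r)] = (1 − r)/2. With SD 3.5, a 3-point effect and 50 per group, the half-width of the 95% interval is 1.96 × SD × √(2/50):

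| r | change SD | adjusted SD | variance saved | half-width, change → adjusted | power, change → adjusted |
|---|---|---|---|---|---|
| 0.3 | 4.14 | 3.34 | 35% | 1.62 → 1.31 | 95.2% → 99.4% |
| 0.5 | 3.50 | 3.03 | 25% | 1.37 → 1.19 | 99.0% → 99.9% |
| 0.7 | 2.71 | 2.50 | 15% | 1.06 → 0.98 | near 100% for both |

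A simulation of 5,000 trials with 50 per group gave savings of 35%, 23% and 15%. With SD 4, the upper end of the range that the protocol cites, power at r = 0.3 goes from 88.7% to 97.6%.

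**If 3.5 is read as the SD of change** and 3.7–4 as the SD of the score, then r = 1 − 3.5²/(2 × 3.7²) = 0.55 to 1 − 3.5²/(2 × 4²) = 0.62. The saving is then 22% to 19%.

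**If the entry window narrows the baseline SD** (s2 = 3.5), the share saved, (s1 − r·s2)² divided by the change variance, is:

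| s1 | r = 0.3 | r = 0.5 | r = 0.7 |
|---|---|---|---|
| 3.0 | 25.4% | 14.5% | 4.6% |
| 2.5 | 15.9% | 5.8% | 0.0% |
| 2.0 | 7.5% | 0.7% | 3.1% |
| 1.7 | 3.7% | 0.0% | 8.3% |

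Scores spread evenly over 10–15 have SD 1.7.

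Truncation also lowers r, so the fairer calculation holds the slope fixed. With slope 0.5 and unrestricted SD 3.5, the residual variance is 12.25 × 0.75 = 9.19, and the saving is 0.25·s1²/(9.19 + 0.25·s1²):
- s1 = 3.5: 3.06/12.25 = 25%
- s1 = 2.5: 1.56/10.75 = 15%
- s1 = 1.7: 0.72/9.91 = 7%. Here r has fallen to 0.27, where the equal-SD formula would wrongly suggest about 36%.

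**The case against.** The planned model is a standard, unbiased analysis under randomisation, and it matches the stated outcome, the hypotheses on change and the sizing target. At the planned effect there is little power left to gain. All of that stands.

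Four stronger readings are tempting, and the protocol does not support them.
- **A fixed loss of 25–35%.** That range needs r of 0.3–0.5 and equal SDs, neither of which is documented. The background section says that symptoms in pregnancy tend to remain stable, which if anything points away from a low r.
- **A larger loss because of the 10–15 window.** Restriction does weaken the correlation, but by narrowing the baseline SD, and that shrinks the saving. The restriction is probably partial, since it applies to the screening score and the analysed baseline is a later questionnaire.
- **A large rescue of power.** At an assumed 2-point effect with SD 3.5 and 50 per group, power would rise from 67% to 84% (r = 0.3) or from 81% to 90% (r = 0.5). The protocol plans for 3 points, so this only illustrates what happens if the true effect is smaller.
- **Covariates or covariance chosen to favour a result.** The text says that covariate effects are also tested. It does not say that they are kept by significance or that the adjusted estimate is primary. The final covariate list, the rule for choosing between unstructured and compound symmetry, and the degrees-of-freedom method are commonly left to an analysis plan, which is not shown.

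None of this gives a reason to leave out baseline EPDS, which is already collected and is measured before allocation.

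**Conclusion.** The point holds as an efficiency improvement, not as an error. As written, baseline EPDS is a free response in each group, and the primary contrast is a raw change-score comparison that baseline adjustment would match or improve on in large samples.

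The avoidable share of variance is (1 − r)/2 if the SDs are equal, and anything from that down to almost nothing if the entry window has narrowed the baseline SD. With equal SDs at r = 0.3–0.5, the interval would be about 19% to 13% narrower (1 − √0.65 and 1 − √0.75). The practical effect on a 3-point comparison at SD 3.5 is small. The benefit is larger if the SD is nearer 4 or the true effect is below 3 points. A reader should not infer bias or an underpowered primary test from this point.

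**What to change.** Keep the mixed model for EPDS, but constrain the baseline mean to be equal in both groups, with group by time terms only after baseline and an unstructured covariance. Three visits need six covariance parameters, which about 100 women can support. Alternatively, use ANCOVA of second-interview EPDS on group and first-interview EPDS.

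Do the same for MAAS, SCL-90 and PRAQ-R2, each with its own first-interview value. MPAS is collected only postnatally and has no baseline of its own.

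Name in advance any further covariates in the primary model, and do not select them by significance.

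The cost is a few lines of text and SAS code, with no new data and no extra visits. The protocol reports 66 women recruited, recruitment continuing and no interim analysis, so the model could be fixed before outcomes are analysed.

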### Interim analyses {21b}

These are not applicable. No interim analyses will be done in this study.

### Methods for additional analyses (e.g., subgroup analyses) {20b}

The sample size and the subgroups are small. Preliminary analyses are conducted to find out if there are statistically significant differences within and between the study groups.

### Methods in analysis to handle protocol non-adherence and any statistical methods to handle missing data {20c}

Because of the relatively small sample size, imputation will not be carried out.

### Plans to give access to the full protocol, participant-level data and statistical code {31c}

Metadata can be published on the project’s web-page without compromising the participants’ data protection. The metadata includes information on what kind of data has been collected, on what date, from whom, and how. Requests for collaboration are encouraged.

## Oversight and monitoring

### Composition of the coordinating center and trial steering committee {5d}

This is not applicable. The authors of the protocol coordinate this study.

### Composition of the data monitoring committee, its role and reporting structure {21a}

The study group is independent.

### Adverse event reporting and harms {22}

The doctoral student of the research team continuously follows up on the information collected from the questionnaires and contacts the women who have admitted to having self-destructive thoughts or plans or whose score is ≥ 16 on the EPDS. She asks if they have psychiatric or psychological support or whether they have discussed the issue in the Healthy Maternity Clinic. All the women are told about support providers verbally by phone and with a care instruction letter by e-mail. All the women whose EPDS scores are between 10 and 15 are also contacted because they are recruited for the study.

### Frequency and plans for auditing trial conduct {23}

The study group meets regularly to maintain the consistency of the intervention delivery and the interviews. The intervention visits are videotaped, and the intervention delivery is monitored from the video recordings of the meetings of the interventionists. Separate supervisions are organized for the graduate students of psychology to maintain the consistency of the interview technique and to receive support.

### Plans for communicating important protocol amendments to relevant parties (e.g., trial participants, ethical committees) {25}

Any changes in the study protocol must be accepted by the Ethics Committee of the Hospital District of Southwest Finland before enforcement.

### Dissemination plans {31a}

The results will be published in an international open access publication and will be linked to the project’s web page, with a plain-language summary in Finnish. The questionnaire results or the interview analyses will not be reported to the participants personally.

## Discussion

Nonmedical and early relationship-focused therapies should be available to treat prenatal depression because supporting the mother-infant relationship makes it possible to decrease depressive symptoms, improve the subsequent development of the child, and avoid the negative effects of antidepressant medication on infants’ health [13, 34, 35, 43–46]. Psychotherapeutic and psychosocial interventions are effective in treating perinatal depression [91] but require special expertise and resources. Moreover, the reduction in a maternal depressive symptoms alone may not improve parenting or the infant’s well-being [38–41]. Because fetal ultrasound has been considered a promising method to support maternal-fetal attachment [92], an ultrasound-assisted intervention could be a low-threshold type of support and easily feasible in maternity care. Therefore, an ultrasound examination used in an interactive manner may be a potential and cost-effective way to support pregnant women with minor or moderate depressive symptoms.

The strengths of our study are the mixed methods and the longitudinal approach that continues into the postpartum period. Furthermore, the multiprofessional approach enables the support of pregnant women in various ways. A weakness in our randomized controlled trial may be the control group’s participation in the attachment representation interviews, which can be experienced as an intervention itself.

Our aim is to develop an intervention for pregnant women with depressive symptoms using 4D ultrasound in an interactive way. The interactive approach is unique and could be integrated into maternity care with a moderate investment. The core elements of the intervention listening to the mother, personalizing the fetus, and giving emotional support can easily be implemented during routine screening and maternity clinic visits. This intervention could serve as a means for maternity care to help women suffering from minor perinatal depression.

## Trial

The protocol version number is five as of December 7, 2021. The first participant was recruited on September 19, 2018. By December 7, 2021, 66 participants have been recruited. The recruitment will be completed within 2 years.

## Data Availability

The metadata will be published on the project’s web page.

## Appendix 2

The course of the first intervention visit

1. The beginning:
  - Ask, how has your (both fetus and pregnant woman) day been?
  - Ask, when has the woman seen her fetus last?
  - Ask for the wishes regarding the ultrasound examination: Is there something special, that you would like us to look at together?
2. Viewing together with the pregnant woman:
  - The gynecologist doing the ultrasound explains to the woman what is seen on the screen and makes sure, that the woman perceives the picture of the baby well enough.
  - Observing together the movements of the fetus’s hands and feet, mouth (sucking, licking, swallowing), and fetus’s face and facial expressions.
  - In general, the fetus is discussed as an individual person.
  - The gynecologist tells about the observations only in a behavioral level (e.g., fetus puts her/his hand on the cheek – not that fetus is described as thoughtful). This way the mother has been given space to create her own meanings to the fetus’s behavior.
  - Fetus’s position and the position of limbs can be explored.
  - Sensation of the movements can be asked, when the fetus’s movements are seen on the screen.
  - It is possible to ask what the mother thinks the fetus is experiencing or feeling.
  - To ask what feelings and emotions looking at the fetus rise.
3. The end
  - Is there something that you would like us to look at together?
  - How has it felt to look at your fetus this way?
  - In the end, the gynecologist doing the ultrasound explains without medical terminology to the woman/mother/parents her perception of the fetus’s well-being.

The course of the second intervention visit

1. The beginning
  - Ask, how has your (both fetus and pregnant woman) day been?
  - Ask, what kind of thought did arise after the last visit?
  - Ask, has the woman seen her fetus in ultrasound examination between the visits?
  - Ask, how has the pregnancy gone?
  - Ask for the woman’s wishes regarding the viewing, is there something special, that you would like us to look at together?
2. Viewing together with the pregnant woman
  - Observing together the movements of the fetus’s hands and feet, mouth (sucking, licking, swallowing), and fetus’s face and facial expressions.
  - Observation only in the behavioral level.
  - Discuss together, how the fetus’s behavior is similar or different compared to last visit.
  - Observation of fetus’s position and the location of fetus’s body parts in the womb.
  - Ask the woman/mother if she feels the movements when the fetus is visibly in motion in the ultrasound.
  - Focusing more to questions regarding what the pregnant woman thinks her fetus is experiencing or feeling. Ask, what makes you think so?
  - Sometimes you can ask the woman to tell about the feelings that looking the fetus arises.
    - Thoughts about fetus’s personality?
    - Especially, if looking arises negative emotions/thoughts, ask the woman what makes her think that way.
  - If the woman is worried about something, the worry is listened to and reacted to. It is also important to tell the woman, if the answer is not known.
  - Pregnant woman’s positive observations will always be shared.
3. The end
  - Is there still something that you would like us to look at together?
  - How did it feel to look at the fetus?
  - In the end, the gynecologist doing the ultrasound explains without medical terminology to the woman her perception of the fetus’s well-being.

The course of the third intervention visit

1. The beginning:
  - Ask, how has your (both fetus and pregnant woman) day been?
  - Ask, what kind of thoughts did arise after the last visit?
  - Ask, has the woman seen her fetus in ultrasound examination between the visits?
  - Ask, how has the pregnancy gone?
  - Ask for the woman’s wishes regarding the viewing, is there something special, that you would like us to look at together?
2. Viewing together with the pregnant woman:
  - Observing together the movements of the fetus’s hands and feet, mouth (sucking, licking, swallowing), and fetus’s face and facial expressions.
  - Observation only in the behavioral level.
  - Discuss together, how the fetus’s behavior is similar or different compared to the last visit.
  - Observation of fetus’s position and the location of fetus’s body parts in the womb.
  - Ask the pregnant woman if she feels the movements when the fetus is visibly in motion in the ultrasound.
  - Sometimes you can ask what the pregnant woman thinks the fetus is experiencing or feeling.
  - Sometimes you can ask the woman to tell about the feelings that looking at the fetus arises.
  - If the pregnant woman is worried about something, the worry is listened and reacted to. It is also important to tell the woman, if the answer is not known.
  - Pregnant woman’s positive observations will always be shared.
  - It is possible to reflect together on woman’s thoughts about the upcoming childbirth
    - When thinking about pregnancy onwards, how does it feel?
    - What kind of birth do you wish for your fetus and yourself?
    - How are you expecting seeing your fetus?
    - How is the fetus right after delivery?
    - Has looking at the fetus with ultrasound invited any reflections about how is the fetus going to be like? If the mother describes the fetus, it is possible to ask how do the characteristics feel.
3. The end
  - Is there still something that you would like us to look at together?
  - How have you experienced these visits?
  - In the end, the gynecologist doing the ultrasound explains without medical terminology to the woman her perception of the fetus’s well-being.

